## Abstract

**Background:**

The major drawback of the community-based mass drug administration (MDA) approach against schistosomiasis is that treatment is offered blindly without testing for the targeted infection. This partly contributes to the low treatment coverage. One approach to overcome this limitation is to introduce a diagnostic component in the treatment approach. This will improve drug uptake and compliance to treatment. This study is conducted to assess the feasibility and acceptability of integrating point-of-care Circulating Cathodic Antigen (POC-CCA) test to community-based directed MDA in improving treatment coverage and compliance with treatment among adults.

**Methods:**

This is a randomized control community trial in which 30 clusters were randomly assigned to either an intervention or control arm to evaluate two interventions on treatment coverage and compliance with treatment. In each cluster, 150 adult participants were enrolled. Community Health Workers (CHW) in both arms were trained on all aspects of praziquantel (PZQ) distribution and management of mild side effects. In the intervention arm, CHWs had additional training on how to use POC-CCA to diagnose intestinal schistosomiasis. In the intervention arm, participants were tested using POC-CCA test for presence of intestinal schistosomiasis and treated based on test results, while in the control arm, participants were treated with PZQ without testing. The primary outcome measure was the proportion of participants provided with PZQ between the two arms and geographical clusters. Secondary outcomes were prevalence of *S. mansoni* infection based on the POC-CCA test conducted by CHWs, ability of CHWs to use the POC-CCA test accurately and safely and community acceptability of the POC-CCA test results from CHWs. Both quantitative and qualitative techniques have been used to collect data at study endpoint.

**Discussion:**

The study will generate evidence on the importance of integrating a diagnostic component into the community directed MDA conducted by CHWs. Findings will generate discussion on the current MDA policy and practice in Tanzania.

**Trial registration:**

PACTR201804003343404 (25/4/2018).

## Background

Schistosomiasis infection is a neglected tropical disease which is highly prevalent in Sub-Saharan Africa (SSA), and is a major cause of public health burden and economic impact [1, 2]. Within the SSA region, two major forms of schistosomiasis-causing species exist: *Schistosoma mansoni* and *Schistosoma haematobium* which cause intestinal and urogenital schistosomiasis respectively [1]. Of the estimated 258 million people infected with schistosomiasis, 90% (192 million cases) occurs in SSA and 779 million people reside in areas with a high risk of schistosomiasis transmission [2, 3]. In Tanzania, because of the wide distribution of schistosomiasis, the entire population of approximately 45 million people remain at risk of the disease, and in 2012 it was estimated that 51.5% of the population was infected [2, 4]. In Tanzania, *S. mansoni* has remained a major public health concern, especially among communities living along and on Lake Victoria islands, in the north-western region [5, 6]. Disabling morbidities associated with schistosomiasis infection include anaemia, malnutrition, impaired development in childhood due to prolonged inflammation and hepatosplenic morbidities characterized by hepatomegaly, splenomegaly and periportal fibrosis in adulthood [7, 8].

The World Health Organization’s (WHO) strategic plan of 2012 proposed scaling up of mass drug administration (MDA) as a means of controlling schistosomiasis by 2020 [9]. Current control of schistosomiasis in Tanzania is based on preventive chemotherapy using praziquantel, the drug of choice, through mass drug administration programs targeting school-aged children in their school environment [10]. Targeting anthelminthics at school-aged children capitalizes on the fact that the heaviest burden of infection is found in this segment of population [10]. However, the major drawback of the school-based approach is that it does not include non-school-going children and other members of the community [11, 12]. In addition, anti-schistosomiasis drugs are not always available in many of the health facilities in endemic areas [13]. From the public health perspective, any infected individual, regardless of age, may represent as a source of infection to the rest of the population, including treated school children [10]. Thus, to achieve a significant reduction in disease burden, every member of the schistosomiasis endemic areas must be reached by the control interventions [11, 12]. The WHO, having knowledge of this, initiated community directed treatment programs [10], in which individuals selected by communities are trained and participate in distributing drugs to other members of the community not covered by the school based program [10].

To increase treatment coverage, community directed treatment has been implemented as an alternative approach for controlling schistosomiasis in a number of African countries to improve access to treatment for community members not included in mass drug administration program [14, 15]. Through this approach, the WHO recommends 75% treatment coverage at community level [9]. In this approach, Community health workers (CHWs) are actively involved in delivering treatment [14, 15]. However, in many of the community directed interventions against schistosomiasis, treatment coverage does not reach the WHO recommendation of 75% [9]. In Uganda for example, the uptake was 50% [16]. Multiple factors have been described to affect the performance of community directed treatment campaigns in schistosomiasis endemic areas [17–19]. Among the major drawback of this approach, is that treatment is offered blindly without any diagnosis of the targeted infection. This may affect community compliance and uptake of treatment, especially among adults. Alternatively, participants who are diagnosed of the targeted infection are more likely to accept and comply with the treatment compared to those treated without diagnosis. In malaria, use of rapid diagnostic testing by community health workers to diagnose malaria increased adherence to treatment [20, 21]. With the more recent easy availability of praziquantel, coupled with widespread escalation of schistosomiasis control using MDA in sub-Saharan Africa, a decline in schistosomiasis infection prevalence is expected. This expected decline could be accelerated by selective mass treatment rather than mass treatment without establishing the status of the infection using any diagnostic technique particularly among adults living in endemic areas [22, 23]. The integration of a diagnostic component into the community-based MDA using trained community health workers is also likely to reduce overall costs.

Point of care Circulating Cathodic Antigen (POC-CCA) test is a simple rapid test, easy to perform and interpret, as the results based on colour change [24]. The test has been recommended by the WHO for screening of intestinal schistosomiasis in endemic areas [24]. The simple nature of the POC-CCA test in terms of testing and interpreting the results based on color change, offers an opportunity to train even unskilled persons with minimal levels of education to perform the test and give treatment based on the test results. However, despite the availability of this opportunity to train community health workers to diagnose and treat schistosomiasis using the POC-CCA tests, no single study has assessed the use of these tests at community level using community health workers. We therefore have the main question: “does integration of rapid diagnostic test for intestinal schistosomiasis diagnosis performed by community health workers increase the uptake and compliance with treatment in adult populations”?

The pre-existing community health workers participating in MDA campaign at Kome Island offers an opportunity to improve the community-based MDA campaign by introducing a diagnostic component into the program to increase confidence of participants in the campaign and increase uptake of treatment [14]. In addition, the wide use of community health workers to diagnose intestinal schistosomiasis could facilitate diagnosis of the disease in settings with limited health personnel, health facilities and increase treatment coverage. Such an approach would help reduce the burden and transmission of intestinal schistosomiasis in the targeted communities. In this context, the main objective of the present study was to assess if introducing point-of-care Circulating Cathodic Antigen (POC-CCA) rapid test to community based mass drug administration through community health workers will increase access, compliance and coverage to treatment among adult individuals at Kome Island in North-Western Tanzania, an area on the Lake Victoria highly endemic for schistosomiasis.

### Hypothesis, aims and objectives

In this study, we hypothesize that integrating point-of-care Circulating Cathodic Antigen tests in community directed mass drug administration campaigns increases the uptake, compliance and coverage of schistosomiasis treatment among adult individuals above the 75% recommended by the WHO [9]. The general objective of this study was to assess whether integrating point-of-care Circulating Cathodic Antigen rapid diagnostic testing by community health workers during a mass drug administration campaign increases uptake of praziquantel treatment among adult population. To address this objective, this study was conducted at Kome Island located in Buchosa district, northwestern Tanzania, an area around the Lake Victoria highly endemic for schistosomiasis. Clusters (service areas served by community health workers) were randomised to receive praziquantel drug without diagnosis or with diagnosis of intestinal schistosomiasis using POC-CCA test and to receive treatment based on the test result.

Primary objective:-To determine the impact of using point-of-care the circulating cathodic antigens rapid diagnostic test by community health workers to diagnosed intestinal schistosomiasis on the uptake of praziquantel treatment among adult individuals diagnosed with *Schistosoma mansoni* infection.

Secondary objectives:-To assess community health worker’s ability to use point-of-care the Circulating Cathodic Antigen rapid test safely and accurately in diagnosing *Schistosoma mansoni* infection in adult individuals and associated factors.To assess community acceptability and attitude towards the use of a point-of-care diagnostic tool for *Schistosoma mansoni* infection within the context of community directed intervention among adults.To document the experience of community health workers after participating in diagnosis of *Schistosoma mansoni* infection using the point-of-care Circulating Cathodic Antigen rapid test.

## Methods

### Study design and area

A cluster randomized two-arm community trial was conducted, in which clusters were defined as the service population of the community health worker and it involved 30 clusters. The study was conducted at Kome Island located in Buchosa District, North-Western Tanzania (Fig. 1). The Kome Island was purposively selected due to high prevalence of *S. mansoni* infection and existence of a strong CHWs system involved in previous community-based schistosomiasis control projects. According to the population census of 2012, the Kome Island has a population of 38,062. Administratively, it has four wards and 16 villages. It is served by one health centre and two dispensaries. Each village has at least one primary school, with the exception of Isenyi village, which has three primary schools, and four villages with no primary school. The main sources of water are Lake Victoria, natural wells and streams. Schistosomiasis is highly endemic in the area and *Schistosoma mansoni*-related morbidities are quite high among the adult population. Recent records indicate that 42.2% of the adult population had periportal fibrosis, 68% had left liver lobe hepatomegaly and 55.2% had splenomegaly [25].

**Fig. 1 Fig1:**
[figure not shown]
Showing allocation of clusters (sub-villages) included in the study arms at Kome Island, North-western Tanzania. (Map was created using ExpertGPS (version 10.3, ESRI, Inc., Redlands, CA) using layers from ESRI data and Maps 10.1)

Schistosomiasis control activities at Kome Island started in 1989 and focused mainly on research and treatment of infected individuals [14]. From 2005 to 2006, a National Schistosomiasis and soil-transmitted helminths (STH) program, with the support of Schistosomiasis control initiatives, implemented a MDA program targeting primary school children for two years [26]. Between 2009 and 2013, integrated community- and school-based treatment programs were implemented in the area [14]. The most recent round of MDA under national Neglected Tropical Diseases (NTDs) control program was carried out among primary school children in late 2015.

### Community health workers

Community Health Workers (CHWs) are an integral part of the health care system in Tanzania [21, 27]. Community Health Workers are appointed by the community among the village members based on minimum criteria that include ability to read and write clearly, to enable record keeping of health interventions which are undertaken in these communities. Depending on the objective of the program, CHWs receive training on health promotion.

At Kome Island, based on previous projects, each of the then 53 sub-villages had two CHWs (a male and a female). However, currently there are 80 sub-villages, and the present study used existing CHWs previously trained on the community-based MDA campaign [14]. There were 54 newly recruited CHWs for 27 sub-villages who took part in this study.

### Trial summary

The study was designed as a cluster randomized two-arm community trial involving randomly selected sub-villages (clusters) at Kome Island. In the intervention arm, community members were tested for intestinal schistosomiasis by CHWs using the POC-CCA test and treated based on the test result (Fig. 2). In the control arm, per current practice, community members received praziquantel treatment from CHWs without being tested. Table 1 shows a summary of the trial.

**Fig. 2 Fig2:**
[figure not shown]
Flow diagram of trial design and number of sub-villages

**Table 1 Tab1:** Summary of the study profile

Study design	Cluster randomized controlled community trial
Intervention	Community health workers testing for *Schistosoma mansoni* infection using Point-of-care Circulating Cathodic Antigen test before offering treatment
Control	Mass drug administration using praziquantel without testing for *Schistosoma mansoni* infection as per current practice
Primary outcome	Proportion of study participants provided with praziquantel drug (treatment coverage) and geographical cluster (a service area of the community health workers) in the intervention and control arms
Cluster eligibility criteria	Having more than 60 adult individuals served by two community health workers
Inclusion	Individuals aged ≥18 years residing in a study cluster (s), willing to participate and give written informed consent
Exclusion	Pregnant women at the time of treatment, history of adverse reaction to praziquantel and acutely ill at the time of treatment
Sampling eligibility criteria	Residents of the selected clusters or residents of Kome island
Sampling exclusion criteria	Non-resident of the cluster or Kome island as identified by community health workers participating in the study
Sample size per arm	Total sample size (*N* = 4500), Intervention arm (n = 2250) and control (*n* = 2250)

To assess CHWs ability to use the POC-CCA test safely and accurately in the intervention arm, a trained observer (a laboratory technician) visited the study cluster at two, four and six weeks post-training and used a checklist to assess CHWs compliance to safety procedures (Table 2).

**Table 2 Tab2:** Shows the steps required to correctly and safely prepare a Circulating cathodic Antigen rapid diagnostic test

S/no	The steps required to correctly and safely prepare a circulating cathodic antigen test (Critical steps in noted boldface type)	Score
1	Prepare the diagnostic table (cover it with a plastic cover), assemble new test, pippete and gloves	
**2**	**Put on a pair of gloves**	
3	Provide participants with new urine container (s) and instruct them on how to collect urine sample(s) using the provided container	
4	Recording participants demographic information (name, age, sex and village of residence) in the registry when submitting urine sample (s) at the diagnostic table	
**5**	**Receive urine sample from participant (s) label the container with participants identification number and place it in a sample collection dish**	
**6**	**Take Point-of-Care circulating cathodic antigen test kit (s), label it with participants (s) identification number which is similar to the one written on the urine container**	
7	Place the labelled point-of-care circulating cathodic antigen test kit on the table (level surface)	
**8**	**Take the urine container with identification number similar to the one labelled on the point-of-care circulating cathodic antigen test kit and collect urine sample using the enclosed pipette and pour 1–3 drops of urine sample in a test kit well**	
**9**	**Dispose the used pippete in a waste bucket immediately after pouring the urine sample in a test kit**	
**10**	**Dispense 2–3 drops of clearing buffer if provided in a sample well**	
**11**	**Wait for 15–20 min before reading the POC-CCA test result (either positive or negative)**	
**12**	**Read the result correctly (either negative or positive)**	
13	Record the result of the POC-CCA test in the participant register book	
14	Give the test result (s) to participants, and based on the test result, advise them (either to take treatment if results are positive or no treatment if negative)	
15	Dispose of used gloves, desiccant, wrappers and used test kits.	

The bolded sentences shows the most critical steps during preparation and use of the point-of-care circulating cathodic antigen test

At baseline, a quantitative questionnaire was used to collect data on CHW’s and community member’s (heads of households) knowledge about schistosomiasis, the previous community-based MDA strategy, acceptability to be diagnosed for intestinal schistosomiasis by CHWs and treatment with PZQ without being diagnosed for the targeted infection. At the end of the study, qualitative Focus Group Discussions (FGDs) were conducted to assess the experiences of CHWs from both arms after participating in the trial. FGDs were held with selected community members who participated in the study to assess community acceptability and attitudes towards use of POC-CCA test by CHWs.

Randomization of clusters to either intervention or control arms was based on the population size of the adult individuals served by a community health worker. All CHWs serving clusters with less than 60 adult populations were excluded from the study.

Randomization of the CHWs to receive the POC-CCA test plus PZQ or PZQ without POC-CCA testing was performed using the *ralloc* programme in Stata version 13. Community Health Workers was the unit of randomization and the unit of analysis (because CHW were representing each of the sub-villages they served). Thirty clusters (i.e. service population served by CHW) with ≥60 adult population were selected from all eligible clusters to participate in the study. The selected cluster were at least 7–15 km away from each other, regardless of whether they were randomized to be in the control or intervention arm. The cluster encompassed a radius around the CHW of at least 5 km and allowed a buffer zone of at least 5 km between the boundaries of different clusters. Buffer zones between the sites had no activities undertaken to prevent contamination between clusters.

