### Study population and inclusion criteria

Individuals aged 18 years and older residing at Kome Island were enrolled after written informed consent was obtained. Participants were enrolled in the study if: (i) aged 18 years and above (ii) willing to participate and give written informed consent and (iii) living in the study area. Participants were excluded from the study if: (i) pregnant at the time of treatment (ii) history of adverse reaction to praziquantel and (iii) present with serious conditions at the time of treatment and not deemed fit to take treatment.

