### Data collection and follow-up

#### Recording of demographic information of participants and community mobilization

Trained CHWs in both arms recorded all demographic information of the study participants in the provided booklets. Collected demographic information included age, sex, sub-village of residence and history of taking anti-schistosomiasis treatment.

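### The pregnancy and illness exclusions are timed to treatment, which only test-positives reach in the intervention arm, so the coverage denominators can differ by arm

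*Protocol article*

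**What the plan says.** Table 1 lists the exclusions as "Pregnant women at the time of treatment, history of adverse reaction to praziquantel and acutely ill at the time of treatment". The section Study population and inclusion criteria repeats the timing and makes these exclusions from the study, not only from the drug: "Participants were excluded from the study if: (i) pregnant at the time of treatment". Its illness criterion is worded differently: "present with serious conditions at the time of treatment and not deemed fit to take treatment".

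The path to treatment differs by arm. Under Trial summary, intervention adults were "tested for intestinal schistosomiasis by CHWs using the POC-CCA test and treated based on the test result", while in the control arm "community members received praziquantel treatment from CHWs without being tested". Step 14 of Table 2 has the community health worker give the result and "advise them (either to take treatment if results are positive or no treatment if negative".

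Some steps are common to both arms. Enrolment follows consent: "Individuals aged 18 years and older residing at Kome Island were enrolled after written informed consent was obtained". Registration is also common: "Trained CHWs in both arms recorded all demographic information of the study participants in the provided booklets".

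The primary outcome is the share of study participants who are given praziquantel. Data management and analysis counts intervention coverage from those tested and then treated, and control coverage from the registers. It fixes no common denominator.

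**The concern.** A criterion that is judged when treatment is given needs a moment of treatment. Every control adult has one. In the intervention arm a test-negative adult is advised not to take the drug and has none. A pregnant or unfit control adult can therefore be excluded, while a pregnant or unfit test-negative adult in the intervention arm stays a participant. A test-positive adult who is excluded at that point already has a recorded test result.

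Because the primary outcome is a proportion of participants, the rule on who remains a participant is part of its definition. A rule that works differently by arm after randomisation can move the comparison without any difference in uptake. The community health worker who would apply the check also knows the arm. The two illness wordings add to this, because they could select different adults.

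**Working it through.** **1. The plan's own figure.** Inputs from Sample size: 50% versus 75%, alpha 5%, power 80%, coefficient of variation k = 0.3616, 150 adults per cluster. Hayes–Bennett formula for proportions:

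c = 1 + (1.960 + 0.842)² × [0.5×0.5/150 + 0.75×0.25/150 + 0.3616² × (0.5² + 0.75²)] / 0.25² = 14.71

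This gives 15 clusters per arm, 30 in all and 4500 adults, as stated (two-sided alpha; power at 15 per arm 80.8%). The stated standard deviation also agrees: 0.3616 × 0.625 = 0.226.

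**2. Inputs for the denominators.** Let e be the share of presenting adults who are pregnant or unfit, π the share test-positive, and u the uptake among eligible adults who are offered the drug. The documents give neither e nor π, so I assume e = 2–15% and π = 20–80%, with e independent of π. I take u = 75%, the coverage that the plan assumes for the intervention arm.

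**3. Literal reading, per 150 adults presenting.** Control denominator: 150(1 − e). Intervention denominator: 150(1 − eπ). The difference is 150·e·(1 − π), which is 0.6 adults at e = 2%, π = 80% and 18 adults at e = 15%, π = 20%. At e = 10%, π = 50% the denominators are 135 and 142.5.

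**4. All participants as denominator.** With the literal rule, intervention coverage is u·π(1 − e)/(1 − eπ). With the same exclusion applied to everyone, it is u·π. The shift in percentage points at u = 75% is:

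| e | π = 20% | π = 50% | π = 80% |
|---|---|---|---|
| 2% | −0.2 | −0.4 | −0.2 |
| 5% | −0.6 | −1.0 | −0.6 |
| 10% | −1.2 | −2.0 | −1.3 |
| 15% | −1.9 | −3.0 | −2.0 |

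Worked example, e = 15%, π = 50%: 0.75 × (0.5 × 0.85/0.925 − 0.5) = 0.75 × (0.459 − 0.500) = −0.030. At full uptake the largest shift is −4.1 points.

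**5. Test-positives only as intervention denominator.** If adults excluded at treatment are removed in both arms, coverage is u in both and the shift is zero. If they are removed in the control arm but kept in the intervention arm, intervention coverage is u(1 − e) and the shift is −0.75·e: −1.5 points at e = 2%, −3.75 at 5%, −7.5 at 10%, −11.25 at 15%.

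**6. Sample size.** Reducing the cluster size from 150 to 127.5 (e = 15%) moves c from 14.71 to 14.77. That is still 15 clusters per arm, with power 80.6%.

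**The case against.** The strongest reply is that the criteria stand beside the inclusion criteria and apply to the study as a whole, so they may simply describe an adult's status at that visit. Testing and treatment shared one agreed site, and the test is read within 15–20 minutes. Table 2 is a checklist for preparing the test, not an enrolment flow. Consent is absent from it too, yet comes before enrolment. Under Quality assurance plan, supervisors checked adherence to the inclusion criteria in both arms. The flow diagram is not shown, and an article condenses its protocol.

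Most of this stands, and it limits the point to what the wording permits. It does not remove the point. The timing rule is stated rather than left out, and nothing in the text places the screen before the test.

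A reader might infer more than the documents support:

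- **That control adults are screened before any study step.** Consent and registration apply in both arms. No passage says that a control adult excluded at treatment is left out of the register.
- **That all three exclusions are affected.** A history of adverse reaction to praziquantel has no time attached.
- **That coverage is biased by 7.5 points.** That needs e = 10% and a mixed handling that no passage states: excluded controls dropped, excluded intervention positives kept.
- **That prevalence is biased as well.** This would need recorded positives to be deleted, which no passage says. The two harms also exclude each other. Among positives, coverage shifts only if late exclusions are kept, and prevalence shifts only if they are removed.

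**Conclusion.** The point holds in a limited form. As written, the pregnancy and illness exclusions can act on every control adult but only on test-positives in the intervention arm, so the primary denominators can differ by arm. Whether they did differ cannot be told from the documents.

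On the assumed ranges and an all-participant denominator, the shift is about 0.2 to 3.0 points at 75% uptake, at most about an eighth of the planned 25-point difference (3.0/25 = 12%). It works against the intervention. With a positives-only denominator it runs from zero to 0.75 times the excluded share, depending on a handling rule that the plan does not state. The sample size is unaffected.

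This is separate from the fact that test-negative adults are not treated, which lowers all-participant coverage in the intervention arm by itself and by more. The two wordings of the illness criterion are a plain inconsistency. Which of them is right is not a statistical question.

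**What to change.** In Table 1 and in Study population and inclusion criteria, state that eligibility on pregnancy and illness is assessed once, at enrolment, before the urine step and in the same way in both arms. Keep the check at treatment for safety, but do not let it remove an enrolled adult from the denominator in either arm. Reconcile the two wordings of the illness criterion.

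The article reports enrolment as done. For data already collected, keep every registered adult in the denominator in both arms, with one rule for those not treated, and compute prevalence over all adults tested. Re-applying the exclusions from the registers cannot be relied on, because pregnancy and illness are not among the register fields that the article lists. The authors should also confirm that adults turned away at treatment were registered alike in both arms, since the rule works only as far as they were.

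The cost is a sentence in each place, with no extra participants or procedures in the analysis. The downside is that a few adults found unfit after enrolment count as untreated, in both arms alike.

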### Data management and analysis

Some parts of the open checklist were coded before entered in the computer for analysis. Collected data were double entered using CSPro and the final data set were stored in MySQL database. Data were screened for consistency and errors corrected. Data analysis will be done using Stata version 15 (Stata Corp, College station, Texas, USA). Descriptive statistics will be used to describe participant’s demographic information. Assessment of uptake of praziquantel treatment will be done by comparing proportion of the outcomes between clusters in the two arms. For the intervention arm, treatment coverage will be assessed based on number of individuals tested and received treatment after diagnosis as registered in the booklets. For the control arm, coverage for praziquantel treatment will be assessed from the CHWs booklets/registers.

Odds ratios (OR) and 95% confidence interval (CIs) will be calculated using random effect logistic regression analysis adjusting for clustering. For assessing safety and accurate use of CCA test by CHWs, percentage of total steps, crucial steps and no-crucial steps performed correctly will be calculated for each observation cycle and a generalized estimating equation (GEE) logistic regression model for panel data will be fitted to identify factors associated with correct performance of at least 90% of the total steps. In addition, pooled mean and median percentage for reading of the 20 photographic results will be calculated for each observation cycle.

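### Clusters are said to be allocated on adult population size, but the stated uptake model does not carry size; clarify how it was used and, if it was an allocation factor, adjust for it

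*Protocol article*

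**What the plan says.** Under Trial summary, the protocol article describes the assignment of clusters to arms: "Randomization of clusters to either intervention or control arms was based on the population size of the adult individuals" served by a community health worker (CHW). The next sentence gives a cut-off: "All CHWs serving clusters with less than 60 adult populations were excluded from the study". The same section names the ralloc programme in Stata but describes no strata, size bands or blocks. It also states: "Community Health Workers was the unit of randomization and the unit of analysis".

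Under Data management and analysis, uptake is addressed in two places. One is a comparison of cluster proportions: "Assessment of uptake of praziquantel treatment will be done by comparing proportion of the outcomes between clusters in the two arms". The other is the model: "Odds ratios (OR) and 95% confidence interval (CIs) will be calculated using random effect logistic regression analysis adjusting for clustering". Clustering is the only adjustment named for uptake, and no sentence rules out further terms.

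Two other sections bear on possible covariates. CHWs in both arms recorded "age, sex, sub-village of residence and history of taking anti-schistosomiasis treatment". On CHW experience, the Community health workers section says: "There were 54 newly recruited CHWs for 27 sub-villages who took part in this study".

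**The concern.** A factor used to balance the arms normally belongs in the analysis. Balancing removes that factor's contribution from the true sampling variance of the treatment effect. An analysis that omits the factor still counts that contribution as unexplained variation between clusters. If the factor is related to the outcome, the standard error is then too large, the test rejects less often than its nominal level, and power is lost.

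This deserves attention here because almost all the planned variance lies between clusters. Enrolling more adults per cluster would gain little, whereas explaining part of the between-cluster variation gains something at almost no cost.

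**Working it through.** **Inputs from the Sample size section.** Uptake p0 = 0.50 and p1 = 0.75; alpha 5%, taken as two-sided; power 80%; coefficient of variation k = 0.3616; m = 150 per cluster; 30 clusters, so 15 per arm; between-cluster SD 0.226, which equals 0.3616 × 0.625, with 0.625 the mean of 0.50 and 0.75. The share of between-cluster variance explained by size (R²) is not given; 0 to 0.3 is assumed.

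**Step 1: reproduce the plan.** The Hayes–Bennett formula for unmatched clusters is

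c = 1 + (1.96 + 0.8416)² × V / (p1 − p0)², with V = [p0(1 − p0) + p1(1 − p1)]/m + k²(p0² + p1²).

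- Within-cluster part: 0.4375/150 = 0.00292.
- Between-cluster part: 0.3616² × 0.8125 = 0.10624.
- V = 0.10916, so c = 1 + 7.849 × 0.10916/0.0625 = 14.71, rounded up to 15 per arm.
- 30 × 150 = 4500, as stated. With a common SD of 0.226, c = 14.19, which also rounds up to 15.
- Power at 15 per arm: Φ(√(14 × 0.0625/0.10916) − 1.96) = 80.8%. A noncentral t on 28 df also gives 80.8%.

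No covariate enters this calculation. The within-cluster part is 0.00292/0.10916, or about 3% of V, so about 97% is between clusters.

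**Step 2: add one cluster-level term.** Multiply the between-cluster part by (1 − R²), take SE = √(V/15), and use a noncentral t on 27 df.

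| Assumed R² | SE of risk difference | Power |
|---|---|---|
| 0 | 0.0853 | 80.6% |
| 0.1 | 0.0810 | 84.5% |
| 0.2 | 0.0766 | 88.2% |
| 0.3 | 0.0718 | 91.9% |

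If size explains nothing, the term costs 80.8% − 80.6% = 0.2 percentage points.

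**Step 3: what if size really was a stratum?** The simulation used 30 clusters in two assumed size strata of 16 and 14, allocated equally within strata, with SD 0.226, a linear cluster-level analysis and 20,000 runs per setting. R² is here the share of the whole variance of a cluster proportion.

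| Assumed R² | True alpha, unadjusted | True alpha, adjusted | Power, unadjusted | Power, adjusted |
|---|---|---|---|---|
| 0 | 4.9% | 4.9% | 83% | 82% |
| 0.1 | 3.8% | 4.9% | 83% | 86% |
| 0.2 | 3.1% | 5.3% | 84% | 90% |
| 0.3 | 2.1% | 5.2% | 86% | 93% |

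The unadjusted test is conservative whenever size matters. Under true stratification, the gain from adjusting is about 3, 5 and 7 percentage points at R² = 0.1, 0.2 and 0.3. This is less than the step from 80.8% in Step 2, because balancing already helps the unadjusted estimate.

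**The case against.** The strongest objection is to the premise. The only use of size that the article actually describes is the 60-adult cut-off, which Table 1 and the later text of Trial summary treat as eligibility. If the allocation sentence means no more than that, no design factor has been left out. This reading is possible. Against it, the sentence concerns assignment to arms, the cut-off stands separately, and a cut-off applied before randomization cannot assign arms. The text needs clarifying on either reading.

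A second objection is that covariate lists are commonly left to an analysis plan, which is not shown. That stands for covariates in general. It is weaker for a factor that the article itself ties to the allocation.

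A reader might also infer more than the documents support:

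- **That the trial is undersized or its test invalid.** The stated size reproduces without covariates, and omitting a balancing factor errs on the conservative side. Chance imbalance between randomized arms is already covered by the between-cluster variance; it is not bias.
- **That known predictors of uptake are being ignored.** No section says that size, age, sex or treatment history predicts uptake. The individual variables were recorded by CHWs who knew their arm, after allocation; in the intervention arm, Table 2 places the recording of demographics at urine submission.
- **That the confidence interval would narrow by a set amount.** The standard errors above are for a risk difference. The stated measure is an odds ratio from a random-effects model, where adjustment changes the conditional odds ratio. The gain is better described as power.
- **That CHW experience is a ready covariate.** The article does not say how many of the 30 trial clusters had newly recruited CHWs, so the variable might hardly vary.

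**Conclusion.** The point holds in a limited form. The article ties allocation to cluster adult population size and states an uptake model that does not carry it. If size was a stratification or balancing factor and is related to uptake, the stated analysis is conservative and loses power: about 3 to 7 percentage points under true two-level stratification with 10% to 30% of the variance explained. If size is unrelated to uptake, nothing is gained. If size was only an eligibility cut-off, there is no mismatch between design and analysis, only an unclear sentence.

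These sizes rest on an assumed R², an assumed two-stratum layout and a linear cluster-level analysis; none of the three comes from the documents.

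**What to change.** State how adult population size entered the randomization: as strata (with the bands), by another balancing scheme, or only as the 60-adult cut-off.

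If it was an allocation factor, include it in the primary uptake analysis as a cluster-level term, in the form used for allocation, and report the unadjusted result alongside. CHW status (new versus experienced) may be added as one further cluster-level term if it varies among the 30 trial clusters. Keep age, sex and prior treatment out of the primary adjustment.

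The change is a line or two of wording and needs no participant data beyond those planned. The article describes the analysis as still to be done. The cost is one degree of freedom per cluster-level term, out of 28, and an adjusted odds ratio that is conditional on size and should be labelled so.
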